### **Day 56± 3 days: 4 weeks post-vaccination 2, surveillance visit and vaccination 3 Visit 12**

**Before vaccination** the following steps will be taken:

- Countercheck to confirm the identity of the participant
- Review inclusion/exclusion criteria and check of contraindications/precautions
- Record any complaints, symptom-directed physical examination, and examination of the injection site(s) for any abnormalities
- Record vital signs: tympanic temperature
- Collect 5 ml venous blood sample to measure:
  - FBC (EDTA) 2.5 ml.
  - Biochemistry, WB, ELISA, and GIM (Serum) 2.5 ml.
- Give time to calm the child after the blood draw
- Administer the vaccination dose 3 according to SOP

**After vaccination** the following steps must be taken:

- Observe for a minimum of 30 minutes
- Record tympanic temperature
- Assessment of the immediate local and systemic solicited events
- Provide further information on when the next visit should be
- Instruct the guardian to return to the MRU centre immediately should the participant manifest any signs or symptoms they perceive as important.

### **Days 57: 1 day post-vaccination 3 surveillance visits Visit 13**

- Verify and confirm ID of the participant
- Review history for any adverse events
- Targeted physical examination for solicited local and systemic symptoms
- Record tympanic temperature
- Record other signs/symptoms
- Give details of next visit and remind guardian on what to do if case of any problem

### **Days 59: 3 days post-vaccination 2 surveillance clinic visit Visit 14**

- Verify and confirm ID of the participant
- Review history for any adverse events
- Targeted physical examination for solicited local and systemic symptoms
- Record tympanic temperature
- Record other signs/symptoms
- Give details of next visit and remind guardian on what to do if case of any problem

### **Days 58- 62 Post-vaccination surveillance home visits on days 58, 60, 61, and 62 Field worker home visits**

- Complete the field worker home visit card information
- Solicited symptoms

[figure not shown]

- Record tympanic temperature
- Record any adverse events occurring after the last study vaccination
- Provide details on next visit and what to do in case of any problem

**Day 63± 1 days: 7 days post-vaccination 3 surveillance visit**

**Visit 15**

- Verify and confirm ID of the participant
- Review history for any adverse events
- Targeted physical examination for solicited local and systemic symptoms
- Record tympanic temperature
- Record other signs/symptoms
- Give details of next visit and remind guardian on what to do if case of any problem

**Day 70± 2 days: 14 days post-vaccination 3 surveillance visit**

**Visit 16**

- Verify and confirm ID of the participant
- Review history for any adverse events
- Targeted physical examination for solicited local and systemic symptoms
- Record tympanic temperature
- Record other signs/symptoms
- Give details of next visit and remind guardian on what to do if case of any problem

**Day 84 ± 3 days: 4 weeks post-vaccination 3, surveillance visit**

**Visit 17**

- Countercheck to confirm the identity of the participant
- Record any complaints, symptom-directed physical examination, and examination of the injection site(s) for any abnormalities
- Record vital signs: tympanic temperature
- Assessment of the protocol local and systemic solicited events
- Collect 7.5 ml venous blood sample to measure:
  - FBC (EDTA) 2.5 ml.
  - Biochemistry, WB, ELISA, and GIM (Serum) 2.5 ml.
  - Peripheral blood mononuclear cells (PBMC) for memory B-cell ELISPOT 2.5 ml
- Provide further information on when the next visit should be
- Instruct the guardian to return to the MRU centre immediately should the participant manifest any signs or symptoms they perceive as important.

**Follow up visits: Post-vaccination surveillance home visits on days 140, 224, and 308**

*Field worker home visits*

[figure not shown]

These visits will be undertaken to maintain contact with the participants during the long term follow up period, to collect any adverse event information that may have been missed, and remind them of the next protocol activity.

- Complete the field worker home visit card information
- Record any adverse events occurring since the last contact
- If any event has occurred that may be deemed to be serious, bring back the participant to the clinic for investigator evaluation
- Provide details on next visit and what to do in case of any problem.

### **Day 365± 14 days: Study completion visit**

#### **Visit 18**

This visit constitutes the last protocol foreseen visit for each participant. The following steps will be taken during this visit.

- Countercheck to confirm the identity of the participant
- Record any complaints, symptom-directed physical examination, and examination of the injection site(s) for any abnormalities
- Record vital signs: tympanic temperature
- Collect 7.5 ml venous blood sample to measure:
  - FBC (EDTA) 2.5 ml.
  - Biochemistry, WB, ELISA, and GIM (Serum) 2.5 ml.
  - Peripheral blood mononuclear cells (PBMC) for memory B-cell ELISPOT 2.5 ml
- Give time to calm the child after the blood draw
- Review the patient records for any missing information
- If there is any adverse event, it must be treated according to the existing standard of care, and follow up till resolution.
- Give estimated time for when results of the study will be communicated back to the community
- Reassure them maintaining confidentiality, especially of their identity.

## **5.4 Follow-up**

After each vaccination, participants will be observed for local and systemic reactions for a minimum of 30 minutes. Signs and symptoms will be solicited and recorded by the investigators. Participants will further be followed up by trained field workers during the next six days following each vaccination. During these field worker visits, information on the medical condition of the participants will be obtained using a standardised field worker card. Any adverse events occurring during the follow up period will be notified to the investigators and followed until resolution or stabilisation. If any symptom persists beyond the 14-day surveillance period the participant will be followed daily until resolution of the adverse event.

Every effort will be made to ensure compliance with visits. If a participant does not appear for a scheduled clinic visit, the local guide will visit him again and accompany the participant to the clinic centre. If a serious adverse event (SAE) has occurred, appropriate reporting procedures must be followed as described in section 6.

The following is the summary schedule for the planned field worker visits:

- Post vaccination 1: Days 2, 4, 5 and 6

[figure not shown]

- Post vaccination 2: Days 30, 32, 33 and 34
- Post vaccination 3: Days 58, 60, 61 and 62
- Long-term follow up: Days 140, 224 and 308

## 5.5 Unscheduled Visits

Participants will be advised to report to the MRU anytime they feel unwell, regardless of their perceived cause. At such unscheduled visits, a history and physical examination, clinical laboratory tests including malaria smear if indicated, documentation of any AEs, and any other medically indicated diagnostic or therapeutic procedures will be done. These will be recorded as observations in the participant's study record and if the physician finds them to be adverse events, the appropriate CRF sections will be completed.

[figure not shown]

## 6 ADVERSE EVENTS AND REPORTING PROCEDURES

### 6.1 Definitions

Definitions for the terms adverse event (or experience), adverse reaction, and unexpected adverse reaction have previously been agreed to through the ICH-GCP guidelines and by consensus of the more than 30 Collaborating Centres of the WHO International Drug Monitoring Centre (Uppsala, Sweden). Although those definitions can pertain to situations involving clinical investigations, some minor modifications are necessary, especially to accommodate the pre-approval, development environment.

The following definitions, with input from the WHO Collaborative Centre, have been agreed:

#### 6.1.1 Adverse Event (or Adverse Experience AE)

An AE is any untoward medical occurrence in a clinical investigation subject, temporally associated with the use of a medicinal product, whether or not considered related to the medicinal product.

An AE can therefore be any unfavourable and unintended sign (including an abnormal laboratory finding), symptom, or disease (new or exacerbated) temporally associated with the use of a medicinal product. For marketed medicinal products, this also includes failure to produce expected benefits (i.e. lack of efficacy), abuse or misuse.

#### 6.1.2 Adverse Drug Reaction (ADR)

In the *pre-approval clinical* experience with a new medicinal product or its new usages, particularly as the dose(s) may not be established, all noxious and unintended responses to a medicinal product related to any dose should be considered adverse drug reactions.

The phrase "responses to a medicinal product" means that a causal relationship between a medicinal product and an adverse event is at least a reasonable possibility, i.e., the relationship cannot be ruled out.

#### 6.1.3 Unexpected Adverse Drug Reaction

An adverse drug reaction, the nature or severity of which is not consistent with the applicable product information (e.g. Investigator's Brochure for an unapproved investigational medicinal product) is considered as an unexpected adverse drug reaction.

When there is a Serious Adverse Event (SAE) that is unexpected and associated with the use of the medication (Suspected Unexpected Serious Adverse Reaction (SUSAR)), and which occurs during or after treatment, an "expedited report" is to be submitted to the regulatory authority.

Medical and scientific judgment should be exercised in deciding whether "expedited reporting" is appropriate in other situations, such as important medical events that may not be immediately life-threatening or result in death or hospitalisation but may jeopardise the patient or may require intervention to prevent one of the other outcomes listed in the definition above. These should also usually be considered serious.

The purpose of "expedited reporting" is to make regulators, Investigators, and other appropriate people aware of new, important information on serious reactions. Therefore, such reporting will generally involve events previously unobserved or undocumented, and a guideline is needed on how to define an event as "unexpected" or "expected" (expected/unexpected from the

[figure not shown]

perspective of previously observed, not on the basis of what might be anticipated from the pharmacological properties of a medicinal product).

#### 6.1.4 Serious Adverse Event

During clinical investigations, adverse events may occur which, if suspected to be medicinal product-related (adverse drug reactions), might be significant enough to lead to important changes in the way the medicinal product is developed (e.g., change in dose, population, needed monitoring, consent forms). This is particularly true for reactions which, in their most severe forms, threaten life or function. Such reactions should be reported promptly to regulators. Therefore, special medical or administrative criteria are needed to define reactions that, either due to their nature ("serious") or due to the significant, unexpected information they provide, justify expedited reporting. To ensure no confusion or misunderstanding of the difference between the terms "serious" and "severe," which are not synonymous, the following note of clarification is provided:

The term "severe" is often used to describe the intensity (severity) of a specific event (as in mild, moderate, or severe myocardial infarction); the event itself, however, may be of relatively minor medical significance (such as severe headache). This is not the same as "serious," which is based on patient/event outcome or action criteria usually associated with events that pose a threat to a patient's life or functioning. Seriousness (not severity) serves as a guide for defining regulatory reporting obligations

A serious adverse event (experience) or reaction is any untoward medical occurrence that at any dose:

- results in death,
- is life threatening,
- requires inpatient hospitalisation or prolongation of existing hospitalisation,
- results in persistent or significant disability/incapacity, or
- is a congenital anomaly/birth defect.

NOTE: The term "life-threatening" in the definition of "serious" refers to an event in which the patient was at risk of death at the time of the event; it does not refer to an event which hypothetically might have caused death if it were more severe.

Medical and scientific judgment should be exercised in deciding whether expedited reporting is appropriate in other situations, such as important medical events that may not be immediately life-threatening or result in death or hospitalisation but may jeopardise the patient or may require intervention to prevent one of the other outcomes listed in the definition above. *These should also usually be considered serious.*

#### 6.1.5 Clinical laboratory parameters and other abnormal assessments qualifying as adverse events and serious adverse events

Abnormal laboratory findings (e.g., clinical chemistry, haematology, and urinalysis) or other abnormal assessments that are judged by the investigator to be **clinically significant** will be recorded as AEs or SAEs if they meet the definition of an AE, as defined in Section 6.1.1 or SAE, as defined in Section 6.1.4. Clinically significant abnormal laboratory findings or other abnormal assessments that are detected during the study or are present at baseline and significantly worsen following the start of the study will be reported as AEs or SAEs.

The investigator will exercise his or her medical and scientific judgement in deciding whether an abnormal laboratory finding or other abnormal assessment is clinically significant.

[figure not shown]

## 6.2 Safety Monitoring Plan

### 6.2.1 Role of the Safety Monitor:

The Local Safety Monitor (LSM) will be an experienced clinician qualified to evaluate safety data from clinical trials of vaccines. He/she will not be directly involved in the clinical trial and will be based in Lambaréné. All SAEs will be reported to him/her. In exceptional circumstances, for example a death possibly related to vaccination, or under conditions as outlined in below in the safety monitoring plan, he/she will have the authority to suspend vaccination pending discussion with the sponsor and collaborators. He will hold the code-break information and under conditions as outlined below, he will have the authority to unblind individual subjects. All unblinding should be reported immediately to AMANET. The LSM will also pass on his reports to the Data Safety Monitoring Board (DSMB) regularly, during the process of the trial.

Thus the LSM's role will include:

- Acting as the study participants' advocate
- Promptly communicating relevant safety information to the DSMB
- Providing advice to the investigators on whether a set of clinical circumstances in a study warrants formal notification to AMANET and DSMB
- Providing clinical advice on any illness in study participants especially in circumstances in which treatment might influence the course of the trial
- Review all SAEs as outlined above

### 6.2.2 The Data Safety Monitoring Board (DSMB)

An independent DSMB will be constituted by AMANET to review safety data at specified intervals. The membership of the DSMB will include expertise in clinical vaccine trials in malaria endemic settings, paediatrics, and biostatistics. The role of the DSMB is to provide safety oversight over the conduct of the trial. It will review safety continuously during the trial and will advise on progression of the trial. The DSMB will hold conference calls to review the safety data generated from the trial as generated by the investigators using a standard report template up to specific points. The purpose of these conference calls will be to review the accumulated safety data in order to advise whether or not the study integrity remains intact and whether or not there are any safety concerns worth early notice. In the event that the DSMB identifies a safety concern, the collaborative group including the investigators and AMANET and EMVI will review all safety data in order to decide the next step. Senior investigators and representatives from AMANET will be invited to but not obligated to participate in the conference calls during open sessions, which will be followed by closed sessions including only DSMB members.

The investigator will inform the DSMB of:

- All subsequent protocol amendments, informed screening or study consent form changes or revisions of other documents originally submitted for review
- Serious adverse events (SAEs) and Grade 3 adverse experiences occurring during the study, regardless of relationship to the study vaccine
- New information that may affect adversely the safety of the participants or the conduct of the study.

The DSMB may recommend that AMANET put the study on temporary hold pending review of potential safety issues. The DSMB will request additional information from the Principal Investigator as needed and will request any appropriate statistical calculations to support discussions with AMANET. All documentation provided to members of the DSMB for information and review will be treated in a confidential manner. The detailed terms of reference and modus

[figure not shown]

operendi for the DSMB is contained in the separate DSMB charter, which constitutes part of the documentation for this study.

### 6.2.3 Holding Rules

Vaccination will be performed in a randomised plan. After each vaccination, safety data will be provided in tables by the data manager. The safety tables will be reviewed by the DSMB in a blinded manner.

If there are no safety issues noted, the study will proceed as planned. However, if based on the review of the safety data tables provided, 50% of participants in a particular are found to have developed a Grade 3 adverse event, related to vaccination and persisting at Grade 3 for > 48 hours during the 14 follow-up days after vaccination, a decision of individual un-blinding may then be made by DSMB through the Local Safety Monitor. Subsequent vaccination of that group will be put on hold pending discussion with the investigator, and the sponsor.

Within five working days of the Local Safety Monitor placing vaccination of a group on hold, the Sponsor will organise a meeting (via teleconference, or face-to-face) to review and discuss the safety data and the events leading to the hold order. At least two working days prior to this meeting, the Sponsor will disseminate copies of all relevant safety data to all meeting participants.

**Activation of the Holding Rules requires a thorough review by the DSMB of blinded reactogenicity and safety data and discussion with the investigator, and the sponsor.**

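### The only mandatory hold in Protocol 6.2.3 needs five of ten children with a persistent Grade 3 event, so a vaccine-related SAE or anaphylaxis does not by itself pause dosing

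*Protocol*

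**What the plan says.** Protocol 6.2.3 ties a compulsory hold to half of the participants in a group being "found to have developed a Grade 3 adverse event, related to vaccination and persisting at Grade 3 for > 48 hours", counted over a 14-day follow-up window. The noun after the word for the unit is missing, but the next sentence speaks of the group. Review works from tables: "After each vaccination, safety data will be provided in tables by the data manager". The DSMB sees these blinded, and "If there are no safety issues noted, the study will proceed as planned".

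On who acts, 6.2.3 contains two statements. One sets a clock that starts "Within five working days of the Local Safety Monitor placing vaccination of a group on hold". The closing one reads "Activation of the Holding Rules requires a thorough review by the DSMB of blinded reactogenicity and safety data", and adds discussion with the investigator and the sponsor.

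Elsewhere the protocol gives powers rather than duties to pause:

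- 6.2.1, Local Safety Monitor: the two bases for acting are given as "In exceptional circumstances, for example a death possibly related to vaccination, or under conditions as outlined in below in the safety monitoring plan". What follows from either is a permission, not a duty: "he/she will have the authority to suspend vaccination pending discussion with the sponsor and collaborators". All SAEs are reported to the monitor.
- 6.2.2, DSMB: "The DSMB may recommend that AMANET put the study on temporary hold pending review of potential safety issues". The DSMB reviews safety continuously and is told of every SAE and every Grade 3 event, whatever the causality. If it identifies a concern, the investigators, the sponsor and the product owner must review all safety data and decide the next step.
- 3.5.5: the sponsor or PI may terminate for a major safety concern at any time.
- 3.5.3: systemic hypersensitivity bars further doses for the affected child.
- 6.3.7: SAEs are reported within 24 hours. No pause follows from the report.

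**The concern.** The mandatory trigger is built on severity, persistence and a group proportion. That suits reactogenicity. It does not suit the events for which a first paediatric trial most needs an automatic stop. Section 6.1.4 itself separates seriousness from severity, so an SAE need not be Grade 3. The grading table in 6.3.2 covers solicited reactions and has no entry for anaphylaxis, although 1.10.1 names it as a risk. Anaphylaxis is also typically short: if it is no longer at Grade 3 after 48 hours, it does not count even towards the five.

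Two things are at stake. First, after a related SAE or anaphylaxis, whether the next child is vaccinated depends on someone choosing to use a permissive power. Second, tables reviewed after each vaccination inform the next dose; they do not protect children still to be dosed in the same round. No stagger between children and no within-round stop is stated.

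**Working it through.** **Inputs.** Group size 10, three groups, 30 children, 20 of them on GMZ2 (8.2). Threshold 50% (6.2.3). The protocol states no operating characteristic for the rule and no per-child risk of a related SAE or anaphylaxis, so the risk p is an assumption, shown from 0.1% to 20%. Children are taken as independent with the same risk.

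**Step 1: the threshold as a count.** 0.5 × 10 = 5 children. (If the missing noun meant the whole trial, it would be 0.5 × 30 = 15; the following sentence points to the group.)

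**Step 2: chance that the existing trigger is met.** This generously lets every event qualify: at Grade 3, lasting more than 48 hours, after the same dose. For one group, A = P(X ≥ 5) with X binomial (10, p). For either of the two GMZ2 groups, B = 1 − (1 − A)².

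**Step 3: chance that a first-event rule is met.** In the 20 GMZ2 children, C = 1 − (1 − p)^20. In all 30, if the rabies group had the same risk, D = 1 − (1 − p)^30. D is the price, that is, the chance of at least one pause.

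| Assumed p | A: one group | B: either GMZ2 group | C: first event, 20 children | D: first event, 30 children |
|---|---|---|---|---|
| 0.1% | 2.5e-13 | 5.0e-13 | 0.020 | 0.030 |
| 1% | 2.4e-8 | 4.8e-8 | 0.182 | 0.260 |
| 5% | 0.0000637 | 0.000127 | 0.642 | 0.785 |
| 10% | 0.001635 | 0.00327 | 0.878 | 0.958 |
| 20% | 0.0328 | 0.0645 | 0.988 | 0.9988 |

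Example at 10%: B = 1 − (1 − 0.001635)² = 0.00327 and C = 1 − 0.9^20 = 0.878. At the same risk, the chance that a given group has one to four events, and so no mandatory hold from them, is 0.651 − 0.0016 = 0.65.

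**Step 4: does another clause supply the automatic pause?** The monitor has two bases for suspending in 6.2.1. Exceptional circumstances is a judgement, with a death given only as an example. The other basis points to conditions later in the safety monitoring plan, and the only such condition in 6.2.3 is the 50% rule. The DSMB and termination clauses are worded as may. The compulsory step in 6.2.2 is a review, and it begins only once the DSMB has identified a concern. Section 3.5.3 stops one child, not the group.

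**Step 5: same-round exposure.** The synopsis gives two weeks for enrolment, and 5.2 refers to a single day of first vaccination. Neither states how long a dosing round lasts, so the number of children still undosed when an event occurs cannot be derived.

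**The case against.** The strongest reply is that this trial is well supervised. A local monitor receives every SAE and may suspend. The DSMB reviews continuously and hears of every SAE and Grade 3 event. A concern it identifies must go to joint review, SAEs are reported within 24 hours, and doses are 28 days apart. A competent monitor or board would very probably stop after an anaphylaxis. This stands, and it limits the weight of the point.

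A reader might infer that the decision rests on one person alone. The documents do not support that: 3.5.5 lets the sponsor or PI act at any time, and 6.2.2 brings in the DSMB and the collaborating group.

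A reader might also infer that the monitor must wait for the DSMB. That does not clearly follow. Section 6.2.1 puts suspension first and discussion after, and the closing sentence of 6.2.3 governs the holding rules. The awkwardness lies within 6.2.3, which has the monitor placing a group on hold and also makes activation depend on prior DSMB review.

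The table tests a reactogenicity rule on rare events alone. In practice the rule counts any related Grade 3 event, including pain and fever, so other children could help to reach five. Column B is not the chance that the trial would pause, because the discretionary routes also apply. Nor do the documents support risks of 5% to 20%: there was no SAE among 30 naive adults (1.7.4.1), and none of the five SAEs in the 40-participant Gabonese adult trial was judged related (1.7.4.2).

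Finally, the separate DSMB charter named in 6.2.2 is not shown and may already hold an SAE trigger. Section 6.2.3 does not refer to one.

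**Conclusion.** The point holds as a weakness of the mandatory rule, not as an absence of safeguards. On the protocol's text, one to four children with a vaccine-related SAE or anaphylaxis, or any such event that has left Grade 3 after 48 hours, do not by themselves oblige anyone to stop vaccinating. Every other route to a pause is discretionary.

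Over assumed risks of 0.1% to 10%, the rule is met in either GMZ2 group with probability of at most 0.0033, while a first-event rule is met in the 20 GMZ2 children with probability 0.02 to 0.88. These figures rest on independence, a common risk, and the generous assumption that every event meets the Grade 3 and 48-hour conditions. They compare rules and do not predict conduct. The gap extends to children still to be dosed in the same round, but no number can be put on it. The point merits correction because the change is cheap and concerns child safety. Confidence is medium, mainly because of the unseen charter.

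**What to change.** 1. Add to 6.2.3: any SAE judged vaccine-related, or any anaphylaxis, pauses further vaccination, including of children not yet dosed in the current round, pending prompt DSMB review. No 50% or 48-hour condition applies.
2. Name this in 6.2.1 as a condition on which the Local Safety Monitor suspends at once, without prior DSMB review, and exempt this initial pause from the closing sentence of 6.2.3.
3. Keep the 50% rule for reactogenicity and supply its missing noun.
4. Align the DSMB charter, or cite its trigger in 6.2.3 if it already has one.

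**Cost.** Wording only on paper; SAEs already reach the monitor and the DSMB, so no new data are needed. The real price is a temporary pause that may prove unnecessary: column D gives about 3% to 26% at 0.1% to 1% risk, and 79% to 96% at 5% to 10%. Restricting the trigger to related SAEs and anaphylaxis screens out much background illness, but not all. Causality in 6.3.4 counts as yes when a contribution is possible, it is assessed blinded, and these children are exposed to malaria. A pause could also push doses outside the ±3 day windows and remove children from the per-protocol set in 8.3.1, which matters with 10 per group. The primary analysis in 8.4 includes everyone with at least one dose, so those children would stay in it.
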